## 2 . Experiment method

### 2.1 Single-cell transcriptome analysis using scRNA-seq

Analyze the transcriptome of PBMCs from subjects to assess the distribution and expression of immune cells (B cells, plasma cells, NK cells, CD4 T cells, CD8 T cells, myeloid cells, epithelial cells) and changes in specific immune cells' transcriptome expression (cytokine expression, transcription factors, signal pathways) before and after herbal medicine administration. Sample transport and data analysis for scRNA-seq are conducted by ROKIT Genomics. Create scRNA-seq libraries using the Chromium Single Cell 3' Library & Gel Bead Kit v3 (10xGenomics). Nanoliter-scale droplets isolate thousands of cells, reverse transcribe to cDNA, and assign cell barcoding sequences and UMIs to each cDNA molecule. Analyze sequencing data using the Nextseq 550 or Novaseq 6000 platform (Illumina). Present changes in immune-related gene expression before and after herbal medicine administration using various plots (Barplot-Significant mRNAs, Scatter plot, Volcano plot, Hierarchical clustering heatmap) and summarize candidate mRNAs. Transfer remaining samples to the Korea Institute of Oriental Medicine for storage post-data analysis. Verify selected significant markers via real-time qPCR in individual samples.

### 2.2. Immunophenotyping analysis using flow cytometry (FACS)

Thaw single cells preserved at the Korea Institute of Oriental Medicine, identify dead cells using Live/Dead Fixable Cell Stain kit, and compare immune cell distribution and activation markers before and after herbal medicine administration. Stain with fluorochrome-conjugated antibodies (anti-CD3, anti-CD4, anti-CD8, anti-CD19) and analyze via FACS.

### 2.3 Quantitative analysis of cytokines, SARS-CoV-2 specific antibodies, and neutralizing antibody titers in serum

Quantify pro-inflammatory cytokines (IL-8, IL-1beta, IL-6, IL-10, TNF, and IL-12p70) to evaluate the inflammation response and potential sequelae like organ failure post-severe inflammation.

- Compare cytokine levels before and after herbal medicine administration using Cytometric Bead Array kit (BD Biosciences) and FACS at the Korea Institute of Oriental Medicine.
- Measure SARS-CoV-2 specific antibodies in serum using ELISA and HRP-conjugated secondary antibodies at the Korea Institute of Oriental Medicine.
- Assess SARS-CoV-2 neutralizing antibody titers using SARS-CoV-2 Neutralization Detection Kit (GenScript) and plaque reduction neutralization test at Chungbuk National University's biosafety level 3 facility.

## ① Metabolite analysis

Metabolites are various products generated during metabolism, influenced by both endogenous processes and external factors (infection, gut microbiota), affecting a wide range of physiological and biochemical processes. Using LC-MS and GC-MS, obtain metabolite profiles to observe metabolic changes before and after herbal medicine administration.

### 1. Overview of blood metabolomics analysis via mass spectrometry

- Metabolites refer to various products generated during metabolic processes. They include direct metabolic products of organisms as well as those produced by external factors (such as infections and gut microbiota) and have extensive physiological and biochemical impacts. Metabolites are involved in regulating direct mechanisms of action and contribute to homeostasis by modulating bacterial metabolic mechanisms. Therefore, integrating and interpreting information about metabolite mechanisms with existing biological data to propose new analytical approaches is crucial for understanding basic biological functions and diseases. High-resolution mass spectrometers are highly efficient devices for simultaneously analyzing the entire metabolome, often combined with separation methods such as gas chromatography (GC) and liquid chromatography (LC).

### 2. Items to be observed through metabolite analysis

- The types of metabolites analyzed vary according to LC-MS and GC-MS, as shown in the figure below. In this study, both LC-MS and GC-MS analysis methods are selected to obtain metabolic profiles, including primary and secondary metabolites such as alkaloids and derivatives, benzenoids, homogeneous non-metal compounds, lipids and lipid-like molecules, nucleosides, nucleotides, and analogues, organic acids and derivatives, organic nitrogen compounds, organic oxygen compounds, organohalogen compounds, organoheterocyclic compounds, phenylpropanoids, and polyketides, in the serum. These profiles are used to identify metabolic changes before and after herbal medicine administration.

[figure not shown]

| Sample            | Analysis method                                 | Performing institution                                             | Analysis purpose                                                                                          |
|-------------------|-------------------------------------------------|--------------------------------------------------------------------|-----------------------------------------------------------------------------------------------------------|
| Blood/single cell | scRNA -Seq                                      | ROKIT Genomics                                                     | Verify changes in immune-related transcriptome before and after herbal medicine administration            |
|                   | Real - time qPCR                                | Korea Institute of Oriental Medicine                               | Confirm immune-related transcriptome changes before and after herbal medicine administration              |
|                   | Immunophenotyping using flow cytometry ( FACS ) | Korea Institute of Oriental Medicine                               | Verify changes in immune cell distribution before and after herbal medicine administration                |
| Blood/serum       | Cytokine analysis (CBA )                        | Korea Institute of Oriental Medicine                               | Verify changes in cytokine levels in serum before and after herbal medicine administration                |
|                   | SARS-CoV-2 specific antibody analysis           | Korea Institute of Oriental Medicine                               | Verify changes in SARS-CoV-2 specific antibody levels before and after herbal medicine administration     |
|                   | SARS-CoV -2 neutralizing antibody analysis      | Korea Institute of Oriental Medicine/ Chungbuk National University | Verify changes in SARS-CoV-2 neutralizing antibody levels before and after herbal medicine administration |
|                   | Metabolite analysis                             | Korea Institute of Oriental Medicine                               | Verify changes in metabolites before and after herbal medicine administration                             |

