## **2) Purpose of the Study**

The purpose of this study is to conduct a prospective preliminary clinical trial to evaluate the safety and efficacy of an over-the-counter herbal medicine in individuals who experience fatigue as a symptom of Long COVID after recovering from COVID-19. The trial aims to assess the feasibility of the intervention and research design for future large-scale studies. The primary objective is to explore changes in the Fatigue Severity Scale (FSS) after 12 weeks of taking the herbal medicine (Kyungok-go) in patients with Long COVID-related fatigue. The secondary objective is to evaluate the feasibility of the study design by monitoring recruitment rates and dropout rates during the study period. Additionally, the study aims to explore the

impact of the herbal medicine on COVID-19 immune responses and metabolites associated with fatigue in post-COVID-19 patients.

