### 11.2 Dosage and administration of the herbal medicine

The dosage and administration method for the herbal medicine during the study period are as follows:

[Usage/Dosage]

| Code name (herbal medicine name) | usage | One-time administration unit (dose) |
|----------------------------------|-------|-------------------------------------|
| CV 1 ( Jin Kyungok-go)           | ●/○/● | 1 packet ( 22.5g)                   |
| P ( placebo)                     | ●/○/● | 1 packet ( 22.5g)                   |

●Take, ○Do not take

[ Administration method ]

Administer 2 times a day on an empty stomach or between meals as per the specified method.

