  - Blood chemistry: AST, ALT,  $\gamma$ -GTP, ALP, HbA1c (considered diabetes if abnormal), BUN, creatinine, total bilirubin, glucose.
  - Immunology: COVID-19 specific antibody/neutralizing antibody tests, single-cell transcriptome analysis (scRNA seq.) for immune-related gene expression comparison, FACS for immunophenotyping, serum cytokine levels.
  - Metabolomics: primary and secondary metabolite profiling.
- ⑩ Perform a pregnancy test (urine or serum  $\beta$ -hCG) for women of childbearing potential (test results within 28 days of screening can be used).
- ⑪ Participants follow the investigator's instructions for the following evaluations:
  - Fatigue assessment using FSS.
  - Evaluation of whether fatigue symptoms have persisted for more than four weeks.
- ⑫ Confirm inclusion/exclusion criteria.

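### The exploratory metabolite comparison has no rule for compounds that come from the product and no fasting or packet-timing condition for the blood draws

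*Protocol*

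**What the plan says.** Section 5, 2) Purpose of the Study adds an exploratory aim to the FSS objective: to examine the "impact of the herbal medicine on COVID-19 immune responses and metabolites associated with fatigue in post-COVID-19 patients". The Visit 0 blood work (11.4.1.1) includes "Metabolomics: primary and secondary metabolite profiling", and the same item recurs at Visit 4 (11.4.1.4). The Schedule Summary also allows this draw at unscheduled visits.

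Within 11.4.2.11, the list of items for metabolite analysis names a long run of compound classes, starting with alkaloids and ending with "organohalogen compounds, organoheterocyclic compounds, phenylpropanoids, and polyketides, in the serum". The use follows directly: "These profiles are used to identify metabolic changes before and after herbal medicine administration". The specimen table gives the same purpose: "Verify changes in metabolites before and after herbal medicine administration". The accompanying overview accepts that metabolites can have outside sources and names infection and gut flora as examples. It does not name the product that participants swallow.

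The blood sampling and separation subsections of 11.4.2.11 fix volume, tubes, transport, cell and serum processing, and storage temperature. They say nothing about food or the last packet. The only mention of an empty stomach is in the dosing text: "Administer 2 times a day on an empty stomach or between meals as per the specified method". That governs how the product is taken, not how blood is drawn.

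**The concern.** The test product is a herbal extract in honey, taken up to the visit at which the second sample is drawn. A broad serum profile can pick up its constituents as well as the body's response to them. If the profile is read before against after, a plant compound that is absent at Visit 0 and present at Visit 4 looks like a metabolic change, although it shows only that the product was taken.

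At stake is the interpretation of the metabolite aim. This is a pilot meant to inform larger studies. A list of apparent fatigue-related metabolites that contains exposure markers would be a poor basis for choosing what to measure next. The sampling conditions deserve separate attention: analysis choices can be made or repaired later, but the fasting state and the time since the last packet are lost if they are not standardised or recorded at the draw.

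**Working it through.** The protocol gives no sample size, power or error rate for the metabolite analysis, so there is no figure to reproduce. The check compares the composition tables, the visit windows and the stated analysis.

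**1. Ingredient mass per packet.** Inputs: the composition tables in 9.1 (printed per 112.5 g) and the 22.5 g packet in 9.2 and 11.2. Formula: listed amount × 22.5/112.5 = listed amount × 0.2.

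- Active: rehmannia juice 39.9 × 0.2 = 7.98 g; poria 12.4 × 0.2 = 2.48 g; ginseng 6.2 × 0.2 = 1.24 g; honey 41.5 × 0.2 = 8.30 g.
- Placebo: high fructose syrup 21.0 × 0.2 = 4.2 g; white sugar 14.0 × 0.2 = 2.8 g; together 7.0 g. The ginseng-named additive is 0.01 × 0.2 = 0.002 g.
- Per day (two packets): honey 16.6 g against syrup plus sugar 14.0 g.

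Caveat: the active ingredients sum to 39.9 + 12.4 + 6.2 + 41.5 = 100.0 g under a heading of 112.5 g, while the placebo ingredients do sum to 112.5 g. If the active table is really per 100 g, the factor is 0.225 and each active figure is 12.5% higher: rehmannia juice 8.98 g, poria 2.79 g, ginseng 1.40 g, honey 9.34 g. The conclusion is the same on either basis.

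**2. Herb exposure before and after, by arm.** Section 7 excludes people who took products with the same ingredients within two weeks before the study (the Summary's list omits this criterion). Section 9.5 prohibits such products during it. Herb-derived compounds should therefore be low at Visit 0 in both arms, stay low in the placebo arm, and can rise in the active arm alone. Write the change in a feature as response plus ingested compound. The between-arm difference in change is then the difference in response plus the ingested compound in the active arm. Subtracting placebo leaves that last term in place.

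**3. Sweeteners and timing.** Both arms take a packet twice daily in the same way, under blinding. The sweetener masses are close: 8.3 g (or 9.3 g) against 7.0 g per packet. Time since the last meal or packet should be balanced by randomisation, so in a between-arm comparison it mostly widens the spread. In a before-after reading it has no such protection. The masses are of ingredients; the documents do not give the sugar content of the honey, juice or syrup.

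**4. How far the last packet can be from the Visit 4 draw.** Visit 3 is day 56 ± 2 (54 to 58) and Visit 4 is day 84 ± 2 (82 to 86). The interval runs from 82 − 58 = 24 days to 86 − 54 = 32 days, against a 28-day supply. Days without product = max(0, interval − 28) = 0 to 4. Assuming full adherence and no packets carried over from Visit 3, the last packet may come just before the draw or about 4 days earlier.

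**5. Does the stated analysis cover this?** Section 14.1 plans ANCOVA between groups for efficacy variables. Metabolites are not among the variables in 14.3.1 or 14.3.2, so that model does not reach them as written. The immunology heading in 11.4.2.11 lists four sampling times tied to administration. It is not stated for metabolites, and it disagrees with the Visit 0 and Visit 4 schedule, so those passages need reconciling in any case.

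**The case against.** The strongest reply is that the protocol states a purpose, not a rule. It does not say which features count as findings. The overview expects interpretation against existing biological knowledge, and the aim is limited to metabolites linked to fatigue. The examples in the background section, lactate and ammonia, are endogenous. Product constituents can be recognised at annotation, or by running product extract after the last visit, and such filtering and the between-arm model may properly sit in a statistical analysis plan that is not shown. The class list may simply describe what the instruments cover.

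Most of this stands. A reader might infer that every before-after difference will be taken as metabolic change, or that ingestion can never be separated from an effect on metabolism. The documents support neither inference: no passage sets such a rule, and product-derived features can be identified later. Nor do they support a claim that sugar intake or sampling time biases the comparison of arms, given the similar loads and the common schedule.

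Two things remain. The sampling conditions belong to the protocol and cannot be recovered at analysis. And a placebo contrast alone, however well modelled, would still show herb-derived compounds as differences between arms.

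**Conclusion.** The point holds in a limited form. As written, the metabolite readout is a before-after comparison of a profile that can contain the product's own constituents, drawn under conditions that are neither fixed nor recorded. Herb-derived compounds are the main problem: they can appear as change in the active arm, and comparison with placebo does not remove them. Meal and packet timing is mainly a source of noise.

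The number of active participants involved is 50 if the draw is made at both sites. It is 30 if the blood sampling text, which places collection within Kyung Hee Medical Center, means that site only; the Schedule Summary gives no site restriction. The conclusion assumes that some product constituents or their derivatives are detectable in serum at Visit 4, which the documents do not quantify. The 0 to 4 day range assumes full adherence and no carried-over packets.

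Metabolites are not among the primary endpoint or the 13 secondary endpoints. FSS, safety and feasibility conclusions are unaffected, and the priority is low.

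**What to change.** - In 11.4.2.11, require both research samples (Visit 0 and Visit 4) to be drawn in the same fasting state, and add a CRF line for the time of the last meal and, at Visit 4 or an unscheduled visit, the last packet. This sets a sampling condition and leaves the dosing instructions alone.
- State the metabolite analysis as a comparison of change between arms, not before-after alone.
- Run CV1 and placebo extracts on the same LC-MS and GC-MS methods. Report features found in either extract separately as exposure markers, and limit the statement about fatigue-related metabolites to endogenous features.
- Reconcile the active composition table, whose ingredients total 100.0 g, with its 112.5 g heading.

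The cost is slightly less convenient visits, one CRF line and a few extra extract runs. The extract runs and the between-arm model can be settled before reporting, but the fasting condition and the CRF line must be in place before samples are drawn.

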**
 Types of human specimens, analytical methods, performing institution and analysis purpose**

#### 11.4.2.12 Assessment of pregnancy and lactation

For women of childbearing age, a  $\beta$ -hCG test is performed using serum or urine tests (sticks). If there are test results within 28 days before herbal medicine administration, this test can be omitted. Women who are menopausal (at least one year of amenorrhea), have undergone a hysterectomy, or have had both ovaries (or fallopian tubes) removed are excluded from the test. The potential for pregnancy and lactation is confirmed verbally.

**11.4.2.13 FSS (Fatigue severity scale )**

The FSS is an index that evaluates fatigue over the past week. The subject assesses it directly using a questionnaire under the guidance of the principal investigator or person in charge. Before the subject evaluates the questionnaire, the examiner explains the evaluation method. It consists of nine items, each scored from 1 to 7, with higher scores indicating more severe symptoms. The FSS score is calculated as the average of the nine items. Based on guidelines and clinical research results on chronic COVID-19 syndrome, a score above 4 is considered to indicate significant fatigue symptoms.[23, 24]

**11.4.2.14 Investigate whether symptoms of fatigue have lasted for more than 4 weeks**

The duration of fatigue symptoms is investigated to confirm whether they have persisted for more than four weeks.

**11.4.2.15 0-100 Visual analogue scale (VAS) of fatigue**

Subjects are asked to mark their average fatigue over the past week. On the 0-100 mm VAS line, 0 means no symptoms, and 100 means very severe symptoms.

**11.4.2.16 Chalder Fatigue Scale(ChFS)**

The Korean version of the Chalder Fatigue Scale is used for evaluation. Scores are divided into total, physical (items 1-7), and mental health (items 8-11) sub-scales[25] .

**11.4.2.17 EQ-5D-5L**

EQ-5D classifies health status profiles into five dimensions with five levels: mobility, self-care, usual activities, pain/discomfort, and anxiety/depression. Levels range from 1 (no problem) to 5 (severe problem). Quality of life scores are calculated using the following equation[26] :

$$\begin{aligned} \text{Quality weight} = & 1 - (0.096 + 0.046 \times M2 + 0.058 \times M3 + 0.133 \times M4 + 0.251 \times M5 + \\ & 0.032 \times S2 + 0.050 \times S3 + 0.078 \times S4 + 0.122 \times S5 + \\ & 0.021 \times U2 + 0.051 \times U3 + 0.100 \times U4 + 0.175 \times U5 + \\ & 0.042 \times P2 + 0.053 \times P3 + 0.166 \times P4 + 0.207 \times P5 + \\ & 0.033 \times A2 + 0.046 \times A3 + 0.102 \times A4 + 0.137 \times A5 + 0.078 \times N4) \end{aligned}$$

(N4: 1 if there is any level 4 or above, otherwise 0; M = Mobility, S = Self-care, U = Usual activities, P = Pain/discomfort, A = Anxiety/depression)

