|  | 
3) FSS Scores at Visits 2 and 3
: Compare the FSS scores between groups at each of these time points.
 
4) ChFS Scores and Subscale Scores at Visits 2, 3, and 4
: Record the total score and separate physical (items 1-7) and mental health (items 8-11) subscale scores, and compare these between groups at each time point.
 
5) EQ-5D-5L Scores at Visit 4
: Calculate and compare the EQ-5D-5L scores between groups at this time point.
 
6) PSQI-K Global Score at Visit 4
: Calculate the total Global score from the 7 component scores on the PSQI-K questionnaire and compare these between groups at this time point.
 
7) K-MOCA Total and Domain Scores at Visit 4
: Calculate the scores for the 7 domains, sum these to obtain the total score, and compare these between groups.
 
8) BDI Scores at Visit 4
: Sum the scores for the 4 domains to obtain the total score and compare these between groups.
 
9) DF, DB, and DF-DB Scores at Visit 4
: Compare these scores between groups at this time point.
 
10) Computerized Neurocognitive Function Test Scores at Visit 4
: Compare the scores from the 5 tests between groups.
 
11) SPPB Test Scores at Visit 4
: Compare the walking speed test, sit-to-stand test, static balance test scores, and the overall score between groups.
 
12) Analysis for Feasibility Evaluation
: Calculate the recruitment rate based on the number of participants recruited during the study period out of the planned number of participants. Calculate the registration rate by dividing the total number of study participants by the total number of screened participants. Calculate and compare the dropout rates and reasons for dropout for the overall study participants and for each group.
 
13) Treatment Success Rate Between the Intervention and Control Groups After 12 Week
 |

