## 14. Statistical Analysis Methods

### 14.1 General principles of result analysis

The primary analysis for efficacy evaluation will use the Full Analysis Set (FAS). Safety evaluations will be conducted using the Safety Set. All statistical tests will be two-sided with a significance level of 5%. For efficacy evaluation, missing data in the FAS will be handled using the Last Observation Carried Forward (LOCF) method for statistical analysis, while all other data will be analyzed as originally recorded.

**Safety Set (SS):** A group of subjects who have received the investigational medicinal product at least once and have undergone at least one safety-related follow-up.

**Full Analysis Set (FAS):** A group of subjects who, in accordance with the ITT principle, have received the investigational medicinal product and have at least one measurement of the primary efficacy variable.

For analyses other than efficacy evaluation, such as feasibility evaluation (e.g., recruitment rate, dropout rate, reasons for dropout), the recruitment rate will be calculated as the number of enrolled subjects divided by the total number of screened subjects (%). Dropout rates and

reasons will be analyzed descriptively for both the entire study and each herbal preparation group.

To compare differences between groups for efficacy variables, ANCOVA will be conducted with the assigned group as the factor and the baseline value as the covariate (two-sided  $p < 0.05$ ). If assumptions of ANCOVA (normality, homoscedasticity) are violated or outliers are observed, Ranked ANCOVA will be performed. For categorical data, frequencies and percentages will be calculated, and comparisons between groups will be made using the Chi-square test or Fisher's exact test (if expected frequency is  $\leq 5$ ). Statistical analyses will be conducted using R-software (latest version) or jamovi software (latest version).

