##### **14.3.2 Secondary efficacy variables**

- 1) Final medication adherence
- 2) Differences in final medication adherence between groups
- 3) FSS scores at visit 2 and visit 3
- 4) ChFS scores and subscale scores at visits 2, 3, and 4
- 5) EQ-5D-5L scores at visit 4
- 6) PSQI-K Global score at visit 4
- 7) K-MOCA total and domain scores at visit 4

- 8) BDI scores at visit 4
- 9) DF score, DB score, and DF-DB score at visit 4
- 10) Computerized neurocognitive test scores at visit 4
- 11) SPPB test scores for walking speed, sit-to-stand test, balance test, and total score at visit 4
- 12) Analysis of recruitment rate, dropout rate, and reasons for dropout for feasibility evaluation
- 13) Treatment success rate in fatigue symptoms after 12 weeks of intervention compared between the treatment and control groups

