**15.1.2 Secondary evaluation variables**

- 1) Final medication adherence  
: The mean, standard deviation, median, minimum, and maximum of the final medication adherence (%) for all subjects after 12 weeks (visit 4 or end of the study) will be presented.
- 2) Differences in final medication adherence between groups  
: The mean, standard deviation, median, minimum, and maximum of the final medication adherence (%) will be calculated and compared between the two groups after 12 weeks of intervention (visit 4 or end of the study).
- 3) FSS scores at visits 2 and 3  
: The FSS scores at each visit will be compared between groups.
- 4) ChFS scores and subscale scores at visits 2, 3, and 4  
: The total score and the subscale scores for physical (items 1-7) and mental health (items 8-11) will be recorded. The total scores and subscale scores at each visit will be calculated and compared between the groups.
- 5) EQ-5D-5L scores at visits 2, 3, and 4  
: The EQ-5D-5L scores will be calculated, and the scores at each visit will be compared between the groups.
- 6) PSQI-K global scores at visits 2, 3, and 4  
: The scores for the 7 components from the PSQI-K questionnaire will be calculated and summed to determine the Global score. The Global scores at each visit will be compared between the groups.
- 7) K-MOCA total and domain scores at visit 4  
: The scores for the 7 domains will be calculated and summed to determine the total score. The total scores will be compared between the groups at visit 4.
- 8) BDI score at visit 4  
: The scores for the 4 domains will be summed to determine the total score, which will be compared between the groups at visit 4.

- 9) DF score, DB score, DF-DB scores at visit 4  
: These scores will be compared between the groups at visit 4.
- 10) Computerized neurocognitive test scores at visit 4  
: The scores for the 5 computerized neurocognitive tests will be compared between the groups at visit 4.
- 11) SPPB test scores for walking Speed, sit-to-stand test, balance test, and total score at visit 4  
: The scores for these 3 tests and the total score will be compared between the groups at visit 4.
- 12) Analysis of recruitment rate, enrollment rate, dropout rate, and reasons for dropout for feasibility evaluation  

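### The EQ-5D-5L equation as printed deducts 0.096 from everyone, so the no-problem profile scores 0.904; the constant was probably meant only for profiles with some problem (minor).

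*Protocol*

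**What the plan says.** Section 11.4.2.17 of the Protocol describes five dimensions with five levels each and then gives the scoring rule: "Levels range from 1 (no problem) to 5 (severe problem). Quality of life scores are calculated using the following equation". The bracket subtracted from 1 opens with the constant, followed by the mobility terms: "1 - (0.096 + 0.046 \times M2 + 0.058 \times M3 + 0.133 \times M4 + 0.251 \times M5". Terms for self-care, usual activities, pain/discomfort and anxiety/depression follow, and then 0.078 times an indicator N4. Level 1 has no coefficient in any dimension. The legend attaches a condition to one term only: "N4: 1 if there is any level 4 or above, otherwise 0". The constant carries no indicator, and no sentence in the protocol gives a separate score for a participant with no problems.

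The score is a secondary efficacy variable. Section 14.3.2 lists "EQ-5D-5L scores at visit 4", and the Summary says "Calculate and compare the EQ-5D-5L scores between groups at this time point". Section 15.1.2 says "The EQ-5D-5L scores will be calculated, and the scores at each visit will be compared between the groups", but item 5 there names visits 2, 3 and 4. For efficacy variables, section 14.1 says "ANCOVA will be conducted with the assigned group as the factor and the baseline value as the covariate", with ranked ANCOVA as the fallback if assumptions fail or outliers appear.

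**The concern.** The equation starts from 1 and takes off decrements for problems. A participant without any problem should then lose nothing, yet the printed rule takes off 0.096. Its starting value of 1 cannot be reached by any answer to the questionnaire.

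The constant also does no work as printed. Taken from every participant at every visit, it cancels from each change and each group difference, and in the ANCOVA the intercept absorbs it. A constant placed among the decrements makes sense as the decrement for having any problem at all, just as N4 is the decrement for having any level 4 or above. On that reading, the condition on the constant was lost when the equation was written down.

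What is at stake is the last step of recovery, from some problem to none. An analyst who codes the equation literally and one who sets the no-problem profile to 1 would get different scores from the same questionnaires. If the arms differ in how many participants reach that profile, the estimated group differences would differ too.

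**Working it through.** **Inputs**, all from the equation in section 11.4.2.17: constant 0.096; level-2 decrements M 0.046, S 0.032, U 0.021, P 0.042, A 0.033; level-5 decrements 0.251, 0.122, 0.175, 0.207, 0.137; N4 decrement 0.078. Level 1 contributes 0. Profiles are written in the order M, S, U, P, A. The protocol states no score for any profile, so there is no printed figure to reproduce.

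**Step 1: range of the printed equation.** Evaluating it over all 5^5 = 3,125 profiles gives:

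- Highest, 11111: 1 − 0.096 = 0.904
- Next highest, 11211: 1 − (0.096 + 0.021) = 0.883
- Lowest, 55555: 1 − (0.096 + 0.251 + 0.122 + 0.175 + 0.207 + 0.137 + 0.078) = 1 − 1.066 = −0.066

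No profile reaches 1.

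**Step 2: what the constant does as printed.** Write each score as 0.904 − d, where d is the sum of the level decrements and the N4 term. A change is (0.904 − d_after) − (0.904 − d_before) = d_before − d_after. The constant is gone, and the same holds for a difference between two group means.

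**Step 3: one participant moving to 11111.** Assume that 11111 is worth 1.000 and every other profile keeps its printed score.

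| Starting profile | Printed score | Gain as printed (0.904 − score) | Gain if 11111 = 1.000 | Share of gain lost |
|---|---|---|---|---|
| 11211 | 0.883 | 0.021 | 0.117 | 0.096/0.117 = 82% |
| 21111 | 0.858 | 0.046 | 0.142 | 0.096/0.142 = 68% |
| 11222 | 0.808 | 0.096 | 0.192 | 0.096/0.192 = 50% |
| 22222 | 0.730 | 0.174 | 0.270 | 0.096/0.270 = 36% |

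The shortfall is 0.096 in each row.

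**Step 4: the group difference at Visit 4.** Let p_T and p_C be the shares at 11111 in the treatment and control groups. The two scorings differ only at that profile, so

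difference with 11111 = 1.000, minus difference as printed = 0.096 × (p_T − p_C).

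The protocol gives no figure for these shares. Over an assumed range:

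| Difference in share at 11111 | Amount left out |
|---|---|
| 0 points | 0 |
| 5 points | 0.096 × 0.05 = 0.005 |
| 10 points | 0.096 × 0.10 = 0.010 |
| 20 points | 0.096 × 0.20 = 0.019 |
| 30 points | 0.096 × 0.30 = 0.029 |

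For scale, one level-2 problem in usual activities is worth 0.021 in the same equation.

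**Step 5: the planned analysis.** If nobody is at 11111 at baseline, the covariate is the same under both scorings. Least squares is linear in the outcome, so the ANCOVA group effect shifts by 0.096 times the baseline-adjusted difference in share. A participant who is at 11111 at baseline would also have a covariate 0.096 too low. Under ranked ANCOVA, with outcome and baseline each replaced by ranks, nothing changes: 11111 is the single top profile whether it scores 0.904 or 1.000, since the next is 0.883.

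**The case against.** The strongest objection is that the protocol nowhere says full health scores 1. Level 1 adds no decrement and the printed maximum is 0.904, and these two facts do not contradict each other. If 0.904 is the intended value for 11111, nobody is under-credited. The value set cited as reference 26 would settle the question, and it is not at hand. This objection stands as a limit on confidence. It does not remove the point, because it leaves a constant that does nothing and a reference value that no one can attain, and both suggest a missing condition.

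A second objection is that the effect on the analysis is small or nil. That also stands. Only participants at 11111 are affected. Few should be there at baseline, because entry requires an FSS score of 4 or higher and section 11.4.2.5 looks for difficulty in at least three of four areas of life. The shares at Visit 4 are assumptions.

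Third, scoring conventions can be left to an analysis plan that is not shown. This carries less weight, because the protocol itself prints the equation and directs that scores be calculated with it.

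A reader might infer more than the documents support:

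- That the step into full health disappears. It shrinks, but a positive gain remains from every starting profile, and 11111 still scores highest.
- That the trial's EQ-5D-5L comparison is necessarily biased toward zero. That requires 11111 to be worth 1, unequal shares at 11111, and an analysis on the score scale.
- That planning of the confirmatory trial is compromised. Section 7 says the results will be used to size future trials, but it does not say that EQ-5D-5L values will be used for this, and no utility-based or economic analysis is described.

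**Conclusion.** The point holds as a minor one, with moderate confidence. It is certain that the equation as printed gives 11111 a score of 0.904, that no profile reaches 1, and that the constant has no effect on any comparison. That the constant was meant only for profiles with some problem is an inference from the form of the equation and from the parallel with N4; the protocol does not say so.

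If full health is worth 1, each transition into 11111 loses 0.096, and the raw Visit 4 difference is understated by 0.005 to 0.029 for assumed differences in share of 5 to 30 percentage points in favour of the better arm. The loss is zero if the shares are equal or the ranked analysis is used. Only this secondary endpoint is touched; the primary FSS endpoint is unaffected.

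**What to change.** First check the equation against the value set cited as reference 26. If the check confirms the reading above, add to section 11.4.2.17 that the quality weight is 1.000 when all five dimensions are at level 1, and that 0.096 is deducted only when at least one dimension is at level 2 or above. Leave the other coefficients and N4 as they are. If the source instead gives 0.904 for 11111, say so explicitly.

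Apply the rule at every visit where the EQ-5D-5L is scored, including baseline. The visit list needs reconciling at the same time: the Summary and section 14.3.2 name Visit 4, and the Schedule Summary shows scheduled assessments at Visits 1 and 4 only, while item 5 of section 15.1.2 names visits 2, 3 and 4.

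The cost is one look at the source, one sentence in the protocol and one line of scoring code. No new data are needed.
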